**Sequential versus quadruple therapy as second- line treatment after failure of standard therapy for Helicobacter pylori infection**

Study protocol

Protocol summary

| 1. PPI( Lansoprazole 30mg x2/day) + amoxicillin 1gx2/day followed by 5 days of PPI(Lansoprazole 30mg x2/day) + two antimicrobial drugs ( Clarithromycin500mg x2/day and Tinidazole 500mg x2/day )  2. quadruple drug regimen (i.e.-14 days of PPI (Lansoprazole 30mg x2/day) + Bismuth Subsalicilate 525mg X4/day + Metronidazole 500mg x3/day + Tetracycline 500mg x4/day or Doxyllin 100mg x2/day ) | Regimens |
| --- | --- |
| Both treatments are approved for the eradication of Helicobacter Pylori | Regulatory status |
| Prospective, randomized, open label trial | Study design |
| The objective is to evaluate the efficacy of sequential therapy, i.e. 5 days of PPI + amoxicillin followed by 5 days of PPI + two antimicrobial drugs( clarithromycin and tinidazole ) versus quadruple drug regimen( i.e.-14 days of PPI+ bismuth + metronidazole + tetracycline ) as second line treatment for Helicobacter pylori eradication | Objective |
| From world experience successful eradication on second line treatment with quadruple therapy is approximately 75 %. We assume a non-inferior eradication rate with second line therapy based on sequential therapy.  In addition we assume better compliance rate (defined as the use of >80% of the prescribed medications) in patients randomized to sequential therapy. | Study hypotheses |
| We are planning to include 258 patients of The Department of Gastroenterology, Soroka Medical Center, and Beer-Sheva, Israel. The study will include consecutive ambulatory patients assessed at Gastroenterological Department, Soroka and family practitioner, who failed standard first line therapy-triple therapy of H.pylori and have indications for eradication of H. pylori. Patients are considered initial treatment failures if histology, rapid urease, 13C-urea breath testing or stool AG test will remain positive despite first-line PPI-based triple therapy. These subjects will be randomized at a 1:1 ratio, by blocks of four. | Number of subjects |
| The primary end points of the study are:   - The eradication rate after second line treatment based on sequential therapy comparative to eradication rate after second line therapy based on quadriple regimen. H.pylori eradication is defined as a negative C-urea breath test beginning 4 weeks after eradication treatment completion. - Rate of compliance to the prescribed therapy (more than 80% of medications used for all medications) | Primary endpoints and measurement |
| Study follow-up period will be 8 weeks. During these 8 weeks the study subjects will be assessed 3 times. | Study follow up |
| The secondary end points:  Adverse effects of sequential and quadruple treatment (taste alteration , peripheral neuropathy, seizures, nausea, vomiting, diarrhea, abdominal pain, allergic reaction, photo sensibility) | Secondary endpoints |
| The sample size calculations will be performed based on the following assumptions:  **Efficacy:**  -Rate of successfully achieved eradication of H.pylori for the standard quadruple therapy is 75%  -Non-inferiority delta of 15%  -Alpha 0.05(one-sided)  -Power 80%  Group sample sizes of 116 and 116 achieve 80% power to detect a statistically significant difference in achieving eradication of H.pylori following the recurrent infection. To accommodate a 10% rate of lost to follow-up we will enroll 258 subjects  **Compliance:**   - In standard therapy group compliance rate is expected to be 60% - We anticipate that in sequential therapy group the compliance rate will be 80%.   With two-sided alpha of 0.05 we have 89% power to detect a significant difference. | Sample size consideration |
| 1.signed informed consent  2.age at least 18 years  3. persisting *H.pylori* infection after at least one course of first-line standard triple therapy (Moxypen, Clarin or Flagyl based) | inclusion criteria |
| 1) history of gastrectomy  2) gastric malignancy, including adenocarcinoma and lymphoma  3) previous allergic reaction to antibiotics (amoxicillin, clarithromycin, metronidazole, tetracycline) and proton pump inhibitors  4) Active upper gastrointestinal bleeding within the previous 1 week  5) contraindications to the treatment drugs  6) Pregnant or lactating women  7) Severe concurrent disease or malignancy | Exclusion criteria |
| [name] , Gastroenterology Department, Soroka Medical Center | Principal study investigator |
| Soroka Clinical Research Center  Head: [name] MD PhD  Email: [contact] | Data management and analysis |
|  | Study monitor |
| Soroka Medical Center, Beer Sheva, Israel | Study site |
| 07/2011  The enrollment is planned to continue for 18 months | Estimated start data and enrollment phase |
|  |  |

Background

Helicobacter pylori s known to play a major contributory role in the pathogeneses of chronic gastritis, peptic ulcers, and gastric malignancies (1). Consequently, great emphasis has been placed on its successful eradication. Many first-line treatments have been employed for this purpose, and the most successful regimens have achieved eradication rates of 75–90% [[2](http://www3.interscience.wiley.com/cgi-bin/fulltext/118536283/main.html,ftx_abs" \l "b2%23b2)].in Israel- in period of 2003-2007- eradication rate-from different sources- was between 57.5-82 %.(18) Treatment of *H pylori* infection is a common problem in many practice settings. The prevalence of *H. pylori* infection has been falling in developed countries bud difficulties with eradication have been increasing as the prevalence of resistant strains of *H.pylori* increase. In Israel during the period of 2002-2006 rate of resistance rise- for metronidazole- 31.4% to 60%-(18)' for clarithromycin- resistance rare in the same period is -8% -65%.(18). Another major problem with antimicrobial treatment regimens for *H. pylori* is adherence with the treatment regimen. Intolerable side-effects with prolonged course of treatment can lead to premature discontinuation of therapy and the development of resistant strains of *H.pylori*. (19). Patients with persistent H. pylori infection, despite antibiotic therapy, present a greater challenge with respect to successful cure [[3](http://www3.interscience.wiley.com/cgi-bin/fulltext/118536283/main.html,ftx_abs" \l "b3%23b3)].

A number of salvage regimens have been evaluated in patients with persistent H. pylori infection. Currently, the internationally recommended salvage therapy for H. pylori infection is a bismuth-based quadruple drug regimen consisting of a proton pump inhibitor (PPI), bismuth salt, metronidazole, and tetracycline for a minimum of 7 days [[4,5](http://www3.interscience.wiley.com/cgi-bin/fulltext/118536283/main.html,ftx_abs" \l "b4%23b4)]. However, a recent pooled analysis of trials conducted to evaluate this regimen as a salvage therapy for persistent H. pylori infection demonstrated a mean treatment failure rate of nearly 25%, and this was substantially higher in some countries [[3, 6](http://www3.interscience.wiley.com/cgi-bin/fulltext/118536283/main.html,ftx_abs" \l "b3%23b3)]. Major causes of bismuth-based quadruple therapy included antibiotic resistance and noncompliance [[7](http://www3.interscience.wiley.com/cgi-bin/fulltext/118536283/main.html,ftx_abs" \l "b7%23b7)]. Poor patient compliance with quadruple therapy is mainly due to its considerable side-effect rates and complicated dosing schedules [[8](http://www3.interscience.wiley.com/cgi-bin/fulltext/118536283/main.html,ftx_abs" \l "b8%23b8)]. Bacterial resistance to metronidazole is also an important element of treatment failure [[7,9–11](http://www3.interscience.wiley.com/cgi-bin/fulltext/118536283/main.html,ftx_abs" \l "b7%23b7)], and primary resistance to metronidazole is relatively common [[12,13](http://www3.interscience.wiley.com/cgi-bin/fulltext/118536283/main.html,ftx_abs" \l "b12%23b12)] and has a negative impact on the effectiveness of quadruple therapy [[7](http://www3.interscience.wiley.com/cgi-bin/fulltext/118536283/main.html,ftx_abs" \l "b7%23b7)]. For this reason, more effective, straightforward, better tolerated alternative regimens are needed. Furthermore, a rapid increase in resistance to clarithromycin [[13](http://www3.interscience.wiley.com/cgi-bin/fulltext/118536283/main.html,ftx_abs" \l "b13%23b13)] has increased the need to establish a more efficient rescue therapy.

A meta- analysis of studies comparing sequential therapy with standard PPI-based triple therapy as first line treatment showed that the eradication rate was higher with sequential therapy. (20) Sequential therapy is a new concept in eradication therapy. With this form of therapy, antibiotics are administered in a sequence rather than all together. The sequential regimen that has been well described is a 10-day treatment consisting of a PPI and **AMOXYCILLIN** 1G (both twice daily) administered for the first 5 days followed by triple therapy, consisting of a PPI, clarithromycin 500mg , and tinidazole 500 mg (all twice daily) for the remaining 5 days . The exact mechanism by which ST (sequential therapy) works is uncertain. Several possibilities exist but all remain unproven at this time. One possibility is that decreasing the bacterial density in the stomach with a drug such as amoxicillin (to which resistance is rare) with the initial 5 days of therapy, improves the efficacy of the subsequently administered combination of clarithromycin and tinidazole. It is known that bacteria can develop efflux channels for clarithromycin, which rapidly transfer the drug out of the bacterial cell, preventing binding of the antibiotic to the ribosome (21). Therefore, another possibility is that amoxicillin acts on the bacterial cell wall and weakens it in the initial phase of treatment thereby preventing the development of efflux channels by weakening the cell wall of the bacterium. A final possibility is that the ST has more advantage due to the number of anti-microbial to which the organism is exposed.

The aim of this study is to evaluate the efficacy of sequential therapy, i.e. 5 days of PPI + amoxicillin followed by 5 days of PPI + two antimicrobial drugs( clarithromycin and tinidazole ) versus quadruple drug regimen( i.e.-14 days of PPI+ bismuth + metronidazole + tetracycline ) as second line treatment of H. pylori . Currently there is none or few date of second line treatment with sequential therapy. The eradication rate of first line (triple) therapy In Israel is70-75 %. We have no data about second line eradication rate in Israel. From world experience successful eradication on second line treatment with quadruple therapy is approximately 70%, we assume to obtain the same or higher eradication rate with second line therapy based on sequential therapy.

Methods

Study objectives:

Primary objectives of this study is to compare safety and effectiveness of the eradication rate after second line treatment based on sequential therapy comparative to eradication rate after second line therapy based on quadruple regimen .

Primary endpoint: H. pylori negative breath test starting 4 weeks after the completion of the treatment.

The secondary end points are the adverse effects of sequential and quadruple treatment (taste alteration, peripheral neuropathy, seizures, nausea, vomiting, diarrhea, abdominal pain, allergic reaction, and photosensitivity) and patient compliance with it. Compliance is considered to be satisfactory when drug intake exceeded 80%.

We are planning to include 258 patients of The Department of Gastroenterology, Soroka Medical Center, Beer-Sheva, Israel. Also we will include at ambulatory patients - with direct referral from family physician or newspaper publicity .

Inclusion criteria are:

1) Age at least 18 years

2) Persisting *H. pylori* infection after at least one course of first-line PPI–Amoxicillin–Clarithromycin or Metronidazole therapy. Patients are considered initial treatment failures if histology, rapid urease, stool Ag or 13C-urea breath testing will remain positive despite first-line PPI-based triple therapy. These tests should be performed during the one year before enrollment in this study.

Exclusion criteria:

1) Age< 18

2) History of gastrectomy

3) Gastric malignancy, including adenocarcinoma and lymphoma

4) Previous allergic reaction to antibiotics (amoxicillin, clarithromycin, metronidazole, and tetracycline) and proton pump inhibitors

5) Active upper gastrointestinal bleeding within the previous 1 week

6) Contraindications to the treatment drugs

7) Pregnant or lactating women

8) Severe concurrent disease or malignancy.

Written informed consent will be obtained from all patients prior to enrolment.

The 258 patients enrolled will be randomized to receive one of the following two treatment regimens for10/ 14 days the patients will be informed of the importance of full compliance, warned of side-effects, instructed to complete treatment, and provided with a contact number, in case of problems. One week after completing these therapies, compliance will be evaluated by a physician during the visit in clinic by direct questioning or pill counting. Compliance is considered to be satisfactory when drug intake exceeded 80%. In addition, at this time all patients will be interviewed for adverse events. *H. pylori* eradication is defined as a negative 13C-urea breath 4-16 weeks after eradication treatment completion [[17](http://www3.interscience.wiley.com/cgi-bin/fulltext/118536283/main.html,ftx_abs" \l "b17%23b17)]. (C-urea breath test- Patients are fasted for 4 h before testing. No test meal will be given, and a pre-dose breath sample is obtained. 75 mg of 13C-urea powder dissolved in 50 mL of water is then administered orally, and a second breath sample is collected 30 minutes later. Collected samples are analyzed using an isotope ratio mass spectrometer). The patient should stop receiving PPI for 10 days before the breath test and not receive any antibiotics for 7days before this exam.

Subject screening and treatment flowchart

Ambulatory patients who failed standard triple first line therapy of H.pylori

Obtain informed consent

Enroll and randomize subjects in two Strata:

1-standard quadruple therapy

2- Sequential therapy

Following drug treatment

For standard quadruple therapy-14 days

For sequential therapy-10 days

First evaluation at one week after completing these therapies

Visit in ambulatory clinic and check

Compliance with treatment and reports of adverse effects

Compliance> 80%-

satisfactory

Compliance < 80% -

Unsatisfactory

Second evaluation -8 weeks after completing treatment

C-urea breath test check the results of

Schedule of events

|  | On enrollment | 7 days after completing treatment –visit in clinic | 8 weeks after completing treatment |
| --- | --- | --- | --- |
| Sign informed consent | X |  |  |
| Check inclusion/exclusion criteria | X |  |  |
| Start one of two treatment regimen  ( sequential or quadruple) | X |  |  |
| Check compliance |  | X |  |
| Ask about adverse effects |  | X |  |
| c-urea breath test |  |  | X |
|  |  |  |  |
|  |  |  |  |

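### Compliance is a primary endpoint in the protocol summary but a secondary endpoint in the Methods, so the trial-level error rate and power depend on which section is followed

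*Protocol*

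**What the plan says.** The protocol gives compliance two different ranks.

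- **Protocol summary, Primary endpoints and measurement.** The row opens in the plural, "The primary end points of the study are", and lists eradication followed by "Rate of compliance to the prescribed therapy (more than 80% of medications used for all medications". The summary's Secondary endpoints row contains adverse effects only.
- **Methods, Study objectives.** One primary endpoint is named: "Primary endpoint: H. pylori negative breath test starting 4 weeks after the completion of the treatment". The next paragraph begins "The secondary end points are the adverse effects of sequential and quadruple treatment" and its list ends with "and patient compliance with it. Compliance is considered to be satisfactory when drug intake exceeded 80" per cent.

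The Sample size consideration row treats the two endpoints separately. Eradication is a non-inferiority comparison: 75% on quadruple therapy, a 15-point margin, one-sided alpha 0.05, 80% power, 116 per arm, and 258 enrolled to allow for 10% loss. Compliance is a superiority comparison of 60% on quadruple with 80% on sequential therapy: "With two-sided alpha of 0.05 we have 89% power to detect a significant difference". The Study hypotheses row also states both expectations, non-inferior eradication and better compliance. No text links the two tests.

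**The concern.** Which endpoints are primary is settled in the protocol, and here it is settled in two ways. An analysis plan written later would have to depart from one section or the other.

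The choice has consequences. Under the Methods, the trial stands or falls on eradication. Under the summary, compliance is a second primary endpoint at full alpha. Depending on how the two are combined, either the error rate rises above 5% or the power for overall success falls below 80%.

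The two endpoints are also not equally hard. The trial is open label, and compliance is judged at a clinic visit by questioning the patient or counting pills. Eradication is a breath-test result. If non-inferiority failed and compliance differed, the summary would leave room to report success on a primary endpoint and the Methods would not. That should be settled before any comparison of the arms is seen.

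**Working it through.** **Inputs** (all from Sample size consideration): eradication 75%, with sequential therapy assumed equal; margin 0.15; one-sided alpha 0.05; power 80%; 116 per arm; 10% loss; compliance 60% v 80%; two-sided alpha 0.05; power 89%.

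**Step 1. Reproduce the stated figures.**

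- Eradication, unpooled variance: n = 2 × 0.75 × 0.25 × (1.645 + 0.842)² / 0.15² = 103.04. With the continuity correction, n/4 × [1 + √(1 + 4/(n × 0.15))]² = 115.99, so 116 per arm. This matches, and power at 116 is 80.0%.
- Enrolment: 232 / 0.90 = 257.8, so 258. This matches.
- Compliance at 116 per arm with continuity correction: the difference is 0.20 − 1/116 = 0.1914; the null standard error is √(2 × 0.70 × 0.30/116) = 0.0602; the alternative standard error is √((0.24 + 0.16)/116) = 0.0587. Power = Φ[(0.1914 − 1.96 × 0.0602)/0.0587] = 89.4%. This matches the stated 89%.

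Each figure is therefore correct for its own endpoint.

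**Step 2. Eradication as sole primary (Methods).** Error is 5% one-sided and power 80%, as stated.

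**Step 3. Two primaries, either suffices.** A false win for sequential therapy can arise from eradication (0.05) or from the upper tail of the compliance test (0.025). Both nulls are taken as true: sequential is 15 points worse on eradication and compliance is equal.

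- Independent tests: 1 − 0.95 × 0.975 = 7.4%.
- Upper bound under any dependence: 0.05 + 0.025 = 7.5%.
- Strongest positive dependence: max(0.05, 0.025) = 5%.
- Power to win at least one, under independence: 1 − 0.20 × 0.11 = 97.8%.

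**Step 4. Two primaries, both required.** Overall success needs both tests, so the error cannot exceed the larger single level, 5%. Joint power is:

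- independent tests: 0.80 × 0.89 = 71.2%;
- lower bound: 0.80 + 0.89 − 1 = 69%;
- upper bound: min(0.80, 0.89) = 80%.

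Without the continuity corrections the separate powers at 116 are 84.0% and 91.9%, and their product is 77.2%, still inside this range. With the corrections, 80% joint power under independence needs about 135 per arm, that is 270/0.90 = 300 enrolled.

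| Reading | Error | Power |
|---|---|---|
| Eradication only | 5% | 80% |
| Either suffices | about 7.4% (at most 7.5%) | about 98% for at least one |
| Both required | at most 5% | about 71% (69% to 80%) for both |

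**The case against.** The strongest reply is that eradication is plainly the main question. The summary's Objective, the aim at the end of the Background and the Methods' primary objective do not mention compliance. The sample size is derived from eradication, and compliance power is reported afterwards. On this view the summary row is a drafting slip. The reply supports the direction of the fix, but the slip does not stand alone: compliance also appears in the Study hypotheses row and has its own alpha and power. The document still supports both readings.

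A second reply is that testing order, alpha split and a both-or-either rule commonly sit in the analysis plan, which is not at hand. That is right, and their absence is not the point here. An analysis plan could supply a rule but could not remove the contradiction from the protocol.

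Three stronger inferences are tempting and should be resisted.

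- *That the trial has neither a 5% error rate nor a defined 80% power.* No single reading breaks both. The either-suffices reading raises error but not power; the both-required reading lowers power but not error control. The 80% is stated for eradication alone and reproduces. The protocol never promises it jointly.
- *That the error could be 9.75%.* The figure 1 − 0.95 × 0.95 counts the compliance tail that favours quadruple therapy, which is not a false win for sequential therapy.
- *That the protocol entitles the sponsor to claim success on compliance alone.* No either-suffices rule is written. The summary only leaves that possibility open. Naming the expected direction in advance is ordinary prespecification.

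Independence is also doubtful. The Background names noncompliance as a major cause of quadruple-therapy failure, so positive correlation is more plausible. That would put joint power between about 71% and 80% and the either-suffices error between 5% and 7.4%.

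**Conclusion.** The contradiction is real and needs correcting: compliance is primary in the summary and secondary in the Methods. The trial-level error rate and power are not fixed until it has one rank. Under the Methods nothing is lost. Under the summary, the cost is an error of about 7.4% (at most 7.5%) if either endpoint suffices, or joint power of about 71% (69% to 80%) if both are required. The central figures assume independent tests, the error figure also assumes that both nulls are true, and the power figure takes the protocol's own 80% and 89% as given. The finding does not question the sample size for eradication, and it does not rest on the absence of a multiplicity rule.

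**What to change.** In the protocol summary, make eradication the single primary endpoint, as the Methods already do. Move compliance to the Secondary endpoints row. In Sample size consideration, label the 89% as power for that secondary comparison. These are wording changes only: one-sided 5%, 80% power and 258 patients are unchanged.

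If a confirmatory compliance claim is wanted, a fixed sequence is one suitable route: test compliance at two-sided 0.05 only after non-inferiority on eradication has been shown. The price is that no confirmatory compliance claim is possible if non-inferiority fails.

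Keeping compliance primary is also workable if both sections say so and state how the endpoints combine, but it costs more. Requiring both needs about 300 enrolled for 80% joint power under independence. Allowing either, with eradication tested at one-sided 0.025, cuts eradication power to about 70% at 116 per arm; restoring 80% needs 144 per arm, or 288/0.90 = 320 enrolled (continuity-corrected).

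### Read per drug, the strict 80% compliance cut-off demands 90% of each sequential antibiotic but only 80.4–82.1% of each quadruple drug, which can shrink and, under some missed-dose patterns, reverse the compliance difference

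*Protocol*

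**What the plan says.** Compliance appears in five places in the protocol.

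- Protocol summary, Primary endpoints and measurement: "Rate of compliance to the prescribed therapy (more than 80% of medications used for all medications".
- Protocol summary, Study hypotheses: sequential therapy is expected to do better, with compliance "defined as the use of >80% of the prescribed medications".
- Methods, Study objectives, and again in the description of the visit one week after treatment: "Compliance is considered to be satisfactory when drug intake exceeded 80" per cent. The Study objectives list compliance among the secondary endpoints.
- Flowchart: one box for above 80% (satisfactory) and one reading "Compliance < 80" per cent (unsatisfactory). Exactly 80% has no box.
- Protocol summary, Sample size consideration: 60% is expected on quadruple therapy, and "We anticipate that in sequential therapy group the compliance rate will be 80" per cent. The stated power is 89% at two-sided 0.05.

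The sequential regimen is "5 days of PPI + amoxicillin followed by 5 days of PPI + two antimicrobial drugs( clarithromycin and tinidazole". Each of these antibiotics is taken twice daily. The quadruple regimen lasts 14 days: PPI twice daily, bismuth four times, metronidazole three times, and either tetracycline four times or doxycycline twice.

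Compliance is assessed by direct questioning or by pill count.

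**The concern.** A percentage cut-off acts on whole doses. Where 80% of a course is a whole number of doses, the choice between above 80% and at least 80% moves the bar by one dose. In a 10-dose course, one dose is 10 percentage points. That situation exists for every sequential drug and for no quadruple drug. A rule worded identically for both arms is then a harder test in one of them.

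The hypothesis is that compliance is better on sequential therapy, and the comparison has its own power statement. A cut-off that is stricter for the sequential arm works against that hypothesis. Part of any observed difference, or of its absence, would come from the cut-off and not from patient behaviour. In an open-label trial, settling the rule after the data are in would also look driven by the results.

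**Working it through.** **1. The plan's own figure.** Inputs from Sample size consideration: p1 = 0.60, p2 = 0.80, n = 116 per arm, two-sided 0.05. With continuity correction:

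z = (0.20 − 1/116 − 1.96·√(2·0.7·0.3/116)) / √((0.24 + 0.16)/116) = (0.1914 − 0.1179)/0.0587 = 1.25, so power is 89.4%.

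This matches the stated 89% (91.9% without the correction). The power figure is correct for 60% versus 80%.

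**2. The bar per drug.** Doses = times per day × days. The bar is the smallest whole count strictly above 80%.

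| Arm | Drug | Doses | 80% of doses | Smallest passing count |
|---|---|---|---|---|
| Sequential | amoxicillin, clarithromycin, tinidazole (each) | 10 | 8.0 | 9 (90%) |
| Sequential | PPI | 20 | 16.0 | 17 (85%) |
| Quadruple | PPI, or doxycycline | 28 | 22.4 | 23 (82.1%) |
| Quadruple | metronidazole | 42 | 33.6 | 34 (81.0%) |
| Quadruple | bismuth, or tetracycline | 56 | 44.8 | 45 (80.4%) |

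One day missed in a sequential phase leaves 8/10 and fails. Two days missed in the quadruple arm leave 12/14 = 85.7% and pass; three leave 11/14 = 78.6% and fail. This step needs only the per-drug reading.

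**3. Size at equal adherence.** The protocol gives no adherence pattern, so these are assumptions. Each patient has a miss probability q, drawn from a beta distribution with mean m of 5–10% and concentration k from 1 (strong variation between patients) to 10 (weak), the same in both arms.

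*Whole days missed.* Sequential passes the strict rule only with no missed day: E[(1−q)^10] = Π((1−m)k+i)/(k+i), i = 0 to 9. For m = 0.10, k = 10 this telescopes to 9/19 = 47.4%. Quadruple passes with at most 2 of 14 days missed.

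- m = 5%, k = 1: 86.2% versus 91.3%, deficit about 5 points.
- m = 10%, k = 10: 47.4% versus 79.4%, deficit about 32 points.
- With at least 80% (at most one missed day per phase), the arms agree within about 2 points at both corners.

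*Single dosing times missed, all drugs due then missed together.* Sequential passes with at most 1 of 10 missed in each phase. Quadruple passes with at most 5 of 28, its tightest schedule.

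- m = 5%, k = 1: 88.7% versus 91.8%, deficit about 3 points.
- m = 10%, k = 10: 61.4% versus 83.8%, deficit about 22 points.
- With at least 80%, the gap is at most about 3 points.

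*Drugs missed independently, no variation between patients* (an extreme case). At 90% per-dose adherence the strict rule gives 0.736³ × 0.867 = 34.6% sequential versus 91.0% quadruple. With at least 80% it gives 0.930³ × 0.957 = 76.9% versus 91.0%. At the adherence that puts quadruple at its planned 60% (86.0% per dose), sequential is 13.9%.

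**4. Early stopping only, constant daily hazard h.** Sequential passes the strict rule if all 10 days are completed, (1−h)^10. With at least 80% it needs 9 days, (1−h)^9. Quadruple needs 12 days, (1−h)^12.

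| h | Sequential, strict | Sequential, at least 80% | Quadruple |
|---|---|---|---|
| 1% | 90.4% | 91.4% | 88.6% |
| 3% | 73.7% | 76.0% | 69.4% |
| 5% | 59.9% | 63.0% | 54.0% |

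The strict cut-off costs the sequential arm about 1–3 points, and it stays ahead.

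**5. Pooled doses.** Sequential has 50 doses and needs 41 (82.0%). Quadruple with tetracycline has 182 and needs 146 (80.2%). Under the whole-day model the deficit is about 0–3 points.

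**The case against.** The best reply is that the per-drug reading is not settled. It rests on the parenthesis in the primary endpoint, which could mean all medications taken together. The hypothesis, Methods and flowchart do not name a unit. On the pooled reading the whole-day effect is small. This stands, and it is why the unit must be stated. Per drug is still the more natural reading of the primary endpoint's wording.

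Second, the lapse that the Background describes is premature discontinuation because of side effects. Under pure early stopping at an equal hazard, the shorter course offsets the higher bar and nothing reverses. This also stands. It limits the claim to scattered missed days or doses.

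Third, one missed dose is 9/10 and passes; failure needs two missed doses of the same drug. The protocol has no data to show that a full missed day is a common lapse.

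A reader might infer that the power for compliance falls from 89% to 27% or less. The documents do not support that. The figure supposes that the planned 80% was set under an at-least-80% rule and that whole days are missed. The protocol defines compliance as above 80% wherever it defines it, and taken as written its 60% and 80% already refer to that rule. It gives no source for either rate. Under early stopping, a sequential rate of 80% on the lenient rule becomes 0.80^(10/9) = 78.0% on the strict one, and power against 60% is still about 81%.

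A reader might also infer that the cut-off must reverse the comparison. It can under some missed-dose patterns, not under all.

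**Conclusion.** The point holds in a limited form. On the per-drug reading the unequal bar is plain arithmetic from the protocol's regimens: 90% of each sequential antibiotic against 80.4–82.1% of each quadruple drug.

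Its effect on the comparison is conditional. At equal adherence, with 5–10% missed and variation between patients, the spurious sequential deficit is about 5–32 points for whole missed days and about 3–22 for single dosing times missed. For early stopping at an equal daily hazard of 1–5% there is no net disadvantage. For pooled doses it is about 0–3 points under the whole-day model. Against a planned difference of 20 points, the rule can shrink the contrast and, under some patterns, erase or reverse it. No single power-loss figure is justified.

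The protocol itself fixes this definition, for an endpoint that its summary calls primary, so it is more than detail left to an analysis plan. It is worth correcting because the change is small. It does not affect the eradication endpoint.

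**What to change.** Define satisfactory compliance as at least 80% in every place: the hypothesis, the primary endpoint, Methods (Study objectives and the one-week visit) and the flowchart, with at least 80% satisfactory and below 80% unsatisfactory. State one unit for both arms, each drug separately or all doses pooled. Make the change before compliance data are compared between arms.

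Either pooling or at least 80% per drug removes most of the artefact. Per drug, some gap from unequal course lengths can remain, as the 76.9% versus 91.0% under independent misses shows.

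The cost is wording only, with two caveats. The cut-off becomes slightly more lenient. And direct questioning, which the protocol allows in place of a pill count, may not separate 8 of 10 from 9 of 10 doses, so the record should show which method was used. The primary listing in the summary and the secondary listing in Methods should be reconciled in the same edit.
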